**Table 2. Aim-specific statistical analysis plan**

| Analysis                                                                        | Subjects analyzed                         | Sample size (15% attrition is expected in power calc.) | Estimated difference based on previous results mean (SD) | Power   | Method                     |
|---------------------------------------------------------------------------------|-------------------------------------------|--------------------------------------------------------|----------------------------------------------------------|---------|----------------------------|
| Between group mean VSS-SF difference @w3, @w6, @m3, @m12                        | All participants                          | 92+92                                                  | 8.1 (7.4) vs 11.5 (9.9)                     | 90%     | ANCOVA                     |
| Between group mean EQ-5D difference until m3                                    | All participants                          | 92+92                                                  | Unknown                                                  | Unknown | Mixed models               |
| Between group mean EQ-5D difference @12m                                        | All participants                          | 92+92                                                  | Unknown                                                  | Unknown | ANCOVA                     |
| Between group mean DHI difference until m3                                      | All participants                          | 92+92                                                  | 24.4 (20.8) vs 29.2 (21.1)                  | 68%     | Mixed models               |
| Mean of means T25-FW (seconds) and timed balance tests (seconds) until m3       | All participants                          | 92+92                                                  | Unknown                                                  | Unknown | Mixed models               |
| Between group mean difference of means of vHIT gain (affected side) @w6 and @m3 | Participants at sites with access to vHIT | 50+50                                                  | 0.52 (0.24) vs 0.69 (0.25) *31                | 99%     | Ranked ANCOVA              |
| Proportion with catch-up saccades                                               | Participants at sites with access to vHIT | 50+50                                                  | Unknown                                                  | Unknown | Binary logistic regression |

|                                                                                                |                        |       |                         |         |                            |
|------------------------------------------------------------------------------------------------|------------------------|-------|-------------------------|---------|----------------------------|
| on vHIT (affected side) @w6 and @m3                                                            |                        |       |                         |         |                            |
| Body sway until m3                                                                             | All participants       | 92+92 | Unknown                 | Unknown | Mixed models               |
| Enhanced body sway analysis (gait analysis) until m3                                           | Umeå participants only | 25+25 | Unknown                 | Unknown | Mixed models               |
| Total steps since last visit @w6 and @m3.                                                      | All participants       | 92+92 | Unknown                 | Unknown | ANCOVA                     |
| Self-reported vestibular rehabilitation compliance until 6w (mean number of training sessions) | All participants       | 92+92 | Unknown                 | Unknown | Mixed models               |
| Proportion with falls or fractures                                                             | All participants       | 92+92 | Unknown                 | Unknown | Binary logistic regression |
| Proportion with BPPV                                                                           | All participants       | 184   | Estimated frequency 10% | N/A     | Binary logistic regression |

Abbreviations: VSS-SF = vertigo symptom scale short form; EQ-5D = EuroQol five-dimension scale; DHI = dizziness handicap inventory; T25-FW = timed 25-foot walk test; SD = standard deviation; vHIT = video head impulse test; @w6 = at 6 weeks; @m3 = at 3 months; @m12 = at 12 months.

\*Power calculations based on mean gain differences before and after vestibular rehabilitation

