| 
1. Compare the impact of the online vestibular rehabilitation tool with standard written instructions after acute onset vertigo on different aspects of everyday living (superiority).
 
2. Compare how the online vestibular rehabilitation tool influences the walking ability and standing balance compared with standard written instructions after acute onset vertigo (superiority).
 
3. Compare how the online vestibular rehabilitation tool influences the lateral canal vestibulo-ocular reflex (VOR) recovery compared with standard written instructions after acute onset vertigo (superiority).
 
4. Compare the long-term effects of early vs. delayed online vestibular rehabilitation on vestibular symptoms and mobility (superiority).
 
5. Compare the effects of online vestibular rehabilitation with standard written instructions on vestibular rehabilitation compliance (superiority).
 
6. Compare the health economic effects of online vestibular rehabilitation with standard written instructions (superiority).
 
7. Compare the kinematic output data from a portable multi-sensor movement analysis system, with the kinematic output data received from the mobile phone app (comparative and partly superiority).
 | 
1. The between groups mean dizziness handicap inventory (DHI) score at 6 weeks and 3 months after vertigo onset.
 
2. The between groups changes in timed 25-foot walk test (T25-FW) from baseline to 6 weeks and 3 months; the between groups body sway during standing and walking; and the mobility at 6 weeks and 3 months after vertigo onset.
 
3. The between groups changes in video head impulse test (vHIT, site-dependent) measured lateral canal VOR gain and saccades from baseline at 6 weeks and 3 months after vertigo onset.
 
4. The between groups mean vertigo symptom scale short form (VSS-SF) score at 12 months after vertigo onset; and the between group pedometer-derived number of steps walked since last visit at 6 weeks and 3 months after vertigo onset.
 
5. The between groups mean number of weekly training sessions at 6 weeks.
 
6. Health economic effects on all levels of care (primary, specialized) and society (sick leave).
 
7. The added-value from using a multi-sensor movement analysis system to receive multi-joint kinematic output, in comparison to using a mobile phone placed on the hip to receive center-of-mass kinematic output.
 |

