## 6.2. Measurements to minimize bias

Subjects will be block-randomized (random blocksize of 4, 6 and 8) 1:1 using site-specific randomization lists generated in R. Randomization will be performed by an independent statistician at Registercentrum Norr. As a precaution measure the lists will contain 4 times as many posts as the expected number of participants at each site. The treatment allocation will be open to the participants and to the site study coordinators, however blinded primary endpoint assessments at week 6 by study coordinators from surrounding sites will be performed as detailed below (section 6.7).

To minimize the risk for an increased effect of rehabilitation mediated by the increased motivation stemming from participating in a clinical trial (in both study arms) the study nurses will be instructed to try to avoid acting as “coaches” and instead concentrate on data collection at the contacts with the participants. This way the effect in the intervention arm will be isolated to the vestibular rehabilitation app, and the effect in the control arm will be isolated to mimic current clinical practice.

Sites will differ according to patient base (e.g., ENT outpatient clinics vs stroke wards). This will entail site mediated differences in participant characteristics. Bias stemming from these differences will be mitigated by including a random effect for site in the primary outcome analysis, and by site stratified randomization.

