### 9.3. Analytical procedures

Two-sided statistical tests will always be performed. The primary outcome will be analyzed using analysis of covariance (ANCOVA) adjusting for baseline measurements; known predictors of the outcome including diagnostic group, sex, age and baseline symptom intensity in order to gain precision in treatment effect estimates; and inclusion of a random effect for site to control for influence from stratified randomization. The primary endpoint results will be reported as the ANCOVA generated adjusted VSS-SF difference with 95% CI and p-value between the study arms at 6 weeks. The VSS-SF has previously been analyzed in a randomized trial assuming normality. If a clear deviation from normality is detected an ordinal logistic regression ANCOVA will be used for the primary outcome.

For secondary outcomes with repeated measurements we will use linear mixed models analysis for continuous outcome variables and binary logistic mixed effects models for binary outcome variables with random effects for individual and site. These techniques can account for repeated measures within an individual and unbalances from missing data. The intervention effect will be modelled using a time by intervention interaction term.

We will also perform statistical validation of the Swedish translation of the VSS-SF questionnaire, including analyses of reliability (test-retest reliability and internal consistency reliability) and validity; construct validity (convergent and discriminant validity) by investigating item-to-item associations between VSS-SF/VSS-SF domains and DHI; and criterion validity by correlating the domains to DHI and balance tests. For the test-retest

study, the first 100 included subjects will complete the evaluator-blinded 6-week assessments of VSS-SF twice, 48 hours apart, via telephone .

Ranked analysis of covariance (ANCOVA) will be used to evaluate intervention effects on T25-FW and VOR gain and saccades, as this method provides robust estimates even though there may be extreme outliers in skewed data. The percentage of participants with sustained improvement in VSS-SF defined as  $\geq 3$  points improvement at 6 weeks and 3 months will also be compared using binary logistic regression.

We will report crude and adjusted analyses, adjusting for baseline values of the studied outcome and the prespecified predictors sex, age, level of education, number of chronic diseases and baseline AVS etiology.

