#### 9.4. Sample size calculation

A change in VSS-SF score of 3 or more has been defined as clinically significant. In an earlier study on a Dutch version of the online vestibular rehabilitation tool on primary care chronic dizziness patients the mean VSS-SF score at three months in the intervention group was 8.1 (SD 7.4), and in the control group 11.5 (SD 9.9). In order to detect a difference in VSS-SF score of 3, assuming a standard deviation of 9 and a correlation between pre and post measurements of 0.6 with 90% power, alpha 5%, we would need n=156 participants, 78 in each arm, using the Shieh sample size calculation method implemented into the Superpower package. Assuming a 15% drop out rate the sample size needs to be increased to n=184 to preserve power. Conservative observational data suggest a yearly incidence of 36 patients with acute onset vertigo and nystagmus per 100,000 inhabitants in the Umeå University uptake area.

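### Table 2's 68% power for the DHI does not follow from the protocol's stated inputs; it matches a calculation at 92 per arm, without the 15% attrition that the column header announces

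*Protocol*

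**What the plan says.** The DHI row of Table 2 (protocol section 9.3) concerns the between-group mean difference up to month 3. It lists 92+92 participants, expected values "24.4 (20.8) vs 29.2 (21.1)", power 68%, and mixed models as the method. The sample-size column is headed "Sample size (15% attrition is expected in power calc.)".

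Section 9.4 fixes the evaluable number: "we would need n=156 participants, 78 in each arm". It then allows for losses: "Assuming a 15% drop out rate the sample size needs to be increased to n=184 to preserve power". The only correlation in the protocol stands in the same section, for the VSS-SF: "assuming a standard deviation of 9 and a correlation between pre and post measurements of 0.6 with 90% power, alpha 5%". No correlation is given for the DHI, either with baseline or between visits.

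Section 9.3 states: "Two-sided statistical tests will always be performed". Section 6.2 gives 1:1 allocation. Section 5.2 makes the DHI the first secondary endpoint, under a superiority objective: "The between groups mean dizziness handicap inventory (DHI) score at 6 weeks and 3 months after vertigo onset". Section 6.3 says that mean DHI is compared between groups at each time point. Section 9.3 models the intervention effect through a time-by-intervention term.

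**The concern.** The header tells the reader that the power figures in the table already allow for 15% loss. If so, the DHI figure should follow from about 78 evaluable participants per arm. It does not do so with the one correlation that the protocol states. It does match a calculation that uses all 92 per arm.

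The stakes are limited but real. A reader of Table 2 would expect about two chances in three of showing the assumed DHI effect. If the true chance for a visit comparison is below one in two, a non-significant DHI result is weaker evidence of no effect than the table implies. The primary analysis, the pass criterion and the sample size do not depend on this cell.

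**Working it through.** **Inputs.**
- Difference: 29.2 − 24.4 = 4.8 (Table 2).
- Pooled SD: √((20.8² + 21.1²)/2) = 20.95 (Table 2).
- Two-sided 5% (sections 9.3 and 9.4), 1:1 allocation (section 6.2).
- Evaluable per arm: 92 × 0.85 ≈ 78, as in section 9.4.
- Correlation 0.6: stated in section 9.4 for the VSS-SF only. Its use for the DHI is an assumption.

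**Formula, one visit.** With n per arm and share R² of the variance explained by baseline, SE = 20.95 × √(1 − R²) × √(2/n), and power ≈ Φ(4.8/SE − 1.96). For a correlation r, R² = r².

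**Reproducing the 68%.** Take 92 per arm and R² = 0.6:
- Adjusted SD = 20.95 × √0.4 = 13.25.
- SE = 13.25 × √(2/92) = 1.954.
- 4.8/1.954 = 2.457, and Φ(2.457 − 1.96) = 69.0%.

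The noncentral t gives 68.6%, and treating the baseline covariate as random, in the manner of the Shieh method cited in section 9.4, gives 68.3%. This matches Table 2.

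**The same R² with the announced attrition (78 per arm).** SE = 13.25 × √(2/78) = 2.122; 4.8/2.122 = 2.262; power 61.9% (t: 61.3%).

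**Correlation 0.6, so R² = 0.36 (78 per arm).** Adjusted SD = 20.95 × 0.8 = 16.76; SE = 2.684; 4.8/2.684 = 1.788; power 43.2% (t: 42.8%; random covariate: 42.5%).

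| Single visit, normal approximation | 78 per arm | 92 per arm |
|---|---|---|
| Unadjusted | 29.8% | 34.2% |
| r = 0.6 | 43.2% | 49.3% |
| R² = 0.6 | 61.9% | 69.0% |

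To reach 68% at 78 per arm with one visit, √(1 − R²) must be 0.589, so R² = 0.653 and r ≈ 0.81.

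**Average of week 6 and month 3.** With baseline correlation r and between-visit correlation ρ, the variance factor is (1 + ρ)/2 − r². At r = 0.6 and 78 per arm:

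| Between-visit ρ | Variance factor | Power (normal; t) |
|---|---|---|
| 0.3 | 0.29 | 75.7%; 75.2% |
| 0.4 | 0.34 | 68.9%; 68.4% |
| 0.5 | 0.39 | 63.0%; 62.4% |
| 0.6 | 0.44 | 57.8%; 57.3% |
| 0.7 | 0.49 | 53.3%; 52.8% |
| 0.9 | 0.59 | 46.1%; 45.7% |

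If one common correlation is used throughout, 68% at 78 per arm needs about 0.72 (68.7%; t: 68.2%).

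**Cross-check on the primary endpoint (section 9.4).** Difference 3, SD 9, 78 per arm:
- R² = 0.6: SE = 9 × √0.4 × √(2/78) = 0.911; power 90.8% (t: 90.5%), which matches the stated 90%.
- r = 0.6: SE = 9 × 0.8 × √(2/78) = 1.153; power 74.0% (t: 73.4%).

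Reading 0.6 as R² therefore reproduces both printed figures: the primary at 78 per arm, and the DHI at 92.

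**The case against.** The strongest reply is that the protocol gives no DHI correlation, so nothing proves 68% wrong. The listed method is a mixed model over two visits. A two-visit average at 78 per arm does reach about 68%, for example with baseline r = 0.6 and between-visit correlation 0.4, or with a common correlation of about 0.72. A mixed model also uses partial data from those who drop out, so 78 complete cases is somewhat cautious, and the further covariates in section 9.3 could add precision. Finally, nothing decisive rests on this cell.

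Much of this stands. A reader might infer that 68% can arise only from an R-squared mix-up with attrition left out; the two-visit examples show that it can arise otherwise. A reader might also infer that the mix-up is proven. It is a fit to printed results, made plausible by the primary sample size, but the calculation itself is not shown. Nor is 43% the DHI power under the plan's own inputs, since 0.6 is stated for another scale.

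Two things remain. The correlations that would rescue 68% appear nowhere in the protocol. And section 6.3 describes a comparison at each time point, for which r would have to be about 0.81 at 78 per arm.

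**Conclusion.** The point holds in a limited form. The 68% does not follow from the stated inputs, and the calculation that it matches most closely (single visit, 92 per arm, R² = 0.6) conflicts with the table's own header on attrition. Keeping that R² and applying the attrition gives about 61-62%. That the correlation of 0.6 was entered as R² is suggested, not established.

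If r = 0.6 is borrowed from the VSS-SF, power at 78 per arm is about 43% per visit. For the two-visit average it is about 57-58% with between-visit correlation 0.6, within a range of about 75% (0.3) to 46% (0.9). The stated 68% lies inside that range, so the averaged figure is undetermined rather than refuted. All these figures take the 4.8-point difference and the SDs in Table 2 as given, and treat attrition as 78 complete cases per arm. The consequence is confined to how a secondary endpoint is read.

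**What to change.** Restate the DHI power cell in Table 2 at 78 per arm, and name the contrast and the assumed correlations beside it. For the per-visit comparison described in section 6.3, that is about 43% at r = 0.6, labelled as carried over from the VSS-SF. If the contrast is the average of week 6 and month 3, give about 57-58% with both correlations at 0.6, together with the range over the between-visit correlation. If the sponsor has DHI correlations of its own, state them and recompute from those.

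The change is one table cell and a short note. This point calls for no change in sample size; the only cost is a less favourable stated figure for a secondary endpoint.

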#### 9.4. Sample size calculation

A change in VSS-SF score of 3 or more has been defined as clinically significant. In an earlier study on a Dutch version of the online vestibular rehabilitation tool on primary care chronic dizziness patients the mean VSS-SF score at three months in the intervention group was 8.1 (SD 7.4), and in the control group 11.5 (SD 9.9). In order to detect a difference in VSS-SF score of 3, assuming a standard deviation of 9 and a correlation between pre and post measurements of 0.6 with 90% power, alpha 5%, we would need n=156 participants, 78 in each arm, using the Shieh sample size calculation method implemented into the Superpower package. Assuming a 15% drop out rate the sample size needs to be increased to n=184 to preserve power. Conservative observational data suggest a yearly incidence of 36 patients with acute onset vertigo and nystagmus per 100,000 inhabitants in the Umeå University uptake area.

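### The inputs printed in section 9.4 give about 73% power with 78 per arm, not 90%; the figure of 78 is reached only if 0.6 is used as R-squared instead of as a correlation.

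*Protocol*

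**What the plan says.** Section 9.4 gives all the inputs of the primary calculation. The aim is stated as "In order to detect a difference in VSS-SF score of 3", "assuming a standard deviation of 9", and then "a correlation between pre and post measurements of 0.6 with 90% power, alpha 5%, we would need n=156 participants, 78 in each arm". The method named is Shieh's ANCOVA sample size method as implemented in the Superpower package. The 156 is raised to 184 for 15% dropout. Section 9.3 settles the sidedness: "Two-sided statistical tests will always be performed".

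Table 2 repeats 90% for VSS-SF at 92+92, but against the means and SDs of an earlier trial, 8.1 (7.4) and 11.5 (9.9). For DHI it gives 68% at 92+92 from "24.4 (20.8) vs 29.2 (21.1"), with mixed models as the method. For vHIT gain it gives 99% at 50+50 from 0.52 (0.24) and 0.69 (0.25), with ranked ANCOVA. The sample-size column header says "15% attrition is expected in power calc". The footnote to the vHIT row reads "Power calculations based on mean gain differences before and after vestibular rehabilitation". No correlation is stated for DHI or vHIT.

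**The concern.** ANCOVA reduces the outcome variance by the square of the pre-post correlation. A correlation of 0.6 removes 36% of it, not 60%. The stated arm size looks too small for the first and right for the second, so the word and the number in section 9.4 seem to describe different quantities.

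The protocol calls this a pivotal confirmatory investigation. If the correlation is as printed, the chance that the significance test misses a true 3-point effect is about 27%, not 10%. A reader weighing a non-significant result would rely on the 90%. The same input seems to lie behind the DHI figure in Table 2, so that table has to be checked too.

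**Working it through.** **Inputs.** Difference 3, SD 9, correlation 0.6, 78 per arm, 90% power and alpha 5% (section 9.4); two-sided (section 9.3); 1:1 allocation (section 6.2).

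**Method.** Residual SD = SD × √(1 − R²). Normal approximation: n per arm = 2 × (1.960 + 1.282)² × residual SD² / difference². The exact figures use the ANCOVA F test with one random covariate, which is the approach section 9.4 names.

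**Reproducing the plan's 78.** Use 0.6 as R-squared.
- Residual variance = 81 × 0.4 = 32.4; residual SD 5.69.
- Normal approximation: 2 × 10.51 × 32.4 / 9 = 75.7, so 76 per arm.
- Exact: 77 per arm gives 89.9%, 78 per arm gives 90.3%. So 78 is the smallest arm size reaching 90%.
- Implied correlation: √0.6 = 0.77.
- Dropout: 156 / 0.85 = 183.5, so 184. This step is correct.

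**The inputs as worded.** Use 0.6 as a correlation.
- R-squared = 0.36; residual SD = 9 × √0.64 = 7.2.
- Normal approximation: 2 × 10.51 × 51.84 / 9 = 121.0, so 122 per arm. Exact: 123 per arm (122 gives 89.9%), or 246 analysed.
- Power at 78 per arm: standard error = 7.2 × √(2/78) = 1.153; 3 / 1.153 = 2.60; 2.60 − 1.96 = 0.64, so 74% by normal approximation and about 73% exactly.
- Power at 92 per arm with nobody lost: 80%.
- Difference detectable with 90% power at 78 per arm: about 3.8 points (3.7 gives 88.9%).

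Other readings at 78 per arm do not rescue 90%: a one-sided test gives 83%, a change score 64%, and no covariate 54%.

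**Table 2, VSS-SF row.** Difference 11.5 − 8.1 = 3.4; pooled SD = √((7.4² + 9.9²)/2) = 8.74. At r = 0.6 this gives 90.5% with 92 per arm and 85.3% with 78 per arm.

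**Table 2, DHI row.** Difference 29.2 − 24.4 = 4.8; pooled SD 20.95. Single-visit ANCOVA gives:

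| Assumption | 78 per arm | 92 per arm |
|---|---|---|
| R-squared 0.6 | 61% | 68.3% |
| r = 0.6 | 43% | 49% |
| no covariate | 29% | 34% |

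Among these, the stated 68% is matched only by R-squared 0.6 with all 92 per arm analysed.

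**Table 2, vHIT row.** Difference 0.69 − 0.52 = 0.17; pooled SD 0.245. At r = 0.6, 50 per arm gives 99.0%. With 42 per arm, roughly what remains after 15% attrition, it gives 97.4%. The arithmetic reproduces.

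**The case against.** **Other covariates.** The primary model also adjusts for diagnostic group, sex and age, so total R-squared could exceed 0.36. That is possible, but section 9.4 credits only the pre-post correlation. The other covariates would have to explain a further 24% of the total variance, and the document offers no basis for that.

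**Table 2's own effect.** At r = 0.6, the earlier trial's 3.4 points and SD 8.74 do give 90% with 92 per arm. This stands, and it means 90% is attainable at r = 0.6 for that effect without attrition. It does not support section 9.4, which powers for 3 points on 78 per arm, and it falls to 85% after the attrition the header says is allowed for.

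**The pass rule.** Section 9.5 defines a pass as an observed difference of at least 3 points. If the true effect is exactly 3, that rule fails about half the time whatever the correlation is. By contrast, significance at r = 0.6 needs an observed difference of only about 2.3 points (1.98 × 1.153). So the 27% is the miss rate of the significance test, not of the pass rule. Section 9.3 also commits to reporting a 95% confidence interval, which limits how far a null result could be over-read.

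**DHI.** A reader might infer that the true DHI power is 43%. The documents do not support that: Table 2 lists mixed models over visits to 3 months and gives no correlation. If the two post-baseline visits are averaged, each with an assumed correlation of 0.6 to baseline, and their mutual correlation is assumed to be 0.6 to 0.8, power is 49–57% at 78 per arm and 56–64% at 92.

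**vHIT.** A reader might also infer that 99% is a calculation error. It is not, as the working shows. What remains open to criticism is the disclosed basis of the figure.

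**Conclusion.** Wrong as written. With a 3-point difference, SD 9, a correlation of 0.6 and a two-sided 5% test, 78 per arm gives about 73% power, not 90%; 90% needs 123 per arm. The exact match at 78 makes it very likely that 0.6 was used as R-squared and then described as a correlation, though the document does not show the calculation itself.

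This does not establish that the trial is underpowered. If R-squared really is 0.6, then 78 per arm is right and only the wording is wrong. The document gives no source for 0.6 under either reading.

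Two secondary points hold in limited form:
- The DHI 68% cannot be matched in single-visit ANCOVA at R-squared 0.6 or r = 0.6 once 15% attrition is taken off, which conflicts with the Table 2 header. Its correct value depends on an unstated correlation and on the mixed model.
- The vHIT 99% is arithmetically sound, but by its own footnote it rests on a change before and after rehabilitation. Under section 6.7 both arms are given the same six exercises, so that change is not an expected difference between arms, which is what the row compares.

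**What to change.** In section 9.4, choose one of the following:
- describe 0.6 as R-squared (r about 0.77) and justify it; or
- keep r = 0.6 and state about 73% power for 3 points with 156 evaluable participants, and 90% for about 3.8 points.

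In Table 2:
- VSS-SF: bring the row into line with section 9.4 and state which difference, SD, correlation and number analysed the 90% refers to.
- DHI: restate the 68% with its correlation, its attrition and the planned mixed model made explicit.
- vHIT: mark 99% as not being the power of the listed between-group comparison, or replace it with unknown.

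The cost is wording and a short recalculation. No change in recruitment is needed to state the power correctly. If r = 0.6 is kept, the stated power becomes less favourable.

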## 6.3. Measurement of variables

The VSS-SF measures the frequency of 15 vestibular symptoms on a scale from 0 (no symptoms) to 4 (symptoms most days) during the past month. The score range is 0–60 and a difference from baseline of  $\geq 3$  points indicate a clinically significant change. The time frame (1 month) for the symptoms will be left as is for the evaluations at week 6 and after 3 months but for the baseline measurement the participants will be asked to report their symptoms during the last 24 hours; and the two response alternatives indicating the highest frequencies (3, quite often [every week] and 4, very often [almost every day]) will be modified to: 3, quite often (almost every hour) and 4, very often (almost all the time). Although this is a deviation from the original version of the VSS-SF this modification is necessary to capture the short-term status of participants soon after vertigo onset. The modified VSS-SF data will be used for the baseline symptom intensity assessments only.

The DHI (range 0–100 points, 0–30 mild, 31–60 moderate and  $\geq 61$  severe dizziness) investigates the effects of dizziness on everyday living. The between group mean DHI score will be compared at each time point as detailed in the statistics section. The scale has subcategories (physical, emotional and functional for DHI) and these will be analyzed separately as exploratory analyses although the total scores will be used for the secondary outcomes.

EQ-5D is an generic instrument which consists of five sub-domains (mobility, self-care, usual activities, pain/discomfort and anxiety/depression) with three severity levels (no, moderate and severe problems). For the current study, the Swedish version EQ-5D-3L will be applied, and the Swedish value set based on experienced health states will be applied to

obtain a health utility score in order to calculate quality-adjusted life years (QALYs). The UK MvH value set will be applied for sensitivity analyses.

The T25-FW data will be collected by using the mean (seconds) of two, timed attempts at walking a clearly marked 25-foot course.

Basic body sway data will be collected by using a locally developed application which utilizes cell phone built-in motion tracking. An enhanced gait analysis with a wearable motion tracking system will be performed at Umeå University Hospital for in-depth measurements.

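### Section 9.4 claims 90% power for a 3-point VSS-SF difference with 78 per arm, but its own inputs give about 73% (156 analysed) to 80% (all 184 analysed)

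*Protocol*

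**What the plan says.** Section 9.4 gives every input to the calculation. The target is set by "In order to detect a difference in VSS-SF score of 3" and the spread by "assuming a standard deviation of 9". The gain from baseline adjustment, the error rates and the resulting size follow in one sentence: "a correlation between pre and post measurements of 0.6 with 90% power, alpha 5%, we would need n=156 participants, 78 in each arm", by the Shieh method in the Superpower package. This is raised to 184 for 15% drop-out.

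Section 9.3 adds "Two-sided statistical tests will always be performed" and names a baseline-adjusted ANCOVA as the primary analysis. Section 6.2 gives 1:1 allocation.

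The VSS-SF row of Table 2 also states 90% power, beside 92+92 participants and "8.1 (7.4) vs 11.5 (9.9"), a difference of 3.4 points. The column header says that 15% attrition is expected in the power calculation.

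Section 6.3 describes the baseline VSS-SF as a modified version, with a 24-hour recall period and changed wording for the two highest response options. It says "The modified VSS-SF data will be used for the baseline symptom intensity assessments only".

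**The concern.** In an ANCOVA, a covariate that correlates r with the outcome removes the fraction r squared of the outcome variance. A correlation of 0.6 removes 36%, not 60%. With 36% removed, 78 per arm looks too few for 90% power at 3 points and SD 9.

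This is the power of the single primary endpoint of a trial that section 3.3 calls pivotal and confirmatory. If the 90% is wrong, a non-significant result would be read as stronger evidence against a 3-point effect than the design can supply. The estimate, its confidence interval and the type I error are not affected.

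**Working it through.** **Inputs.** Difference d = 3, SD = 9, r = 0.6, alpha 5%, target power 90% (9.4). Two-sided test and ANCOVA (9.3). Allocation 1:1 (6.2). Drop-out 15% (9.4).

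**Method.** Exact Shieh-type power with one random covariate and N participants in total: power is the probability that a noncentral F with 1 and N − 3 degrees of freedom exceeds its 5% critical value. The noncentrality is λB, with λ = (N/4) × d² / [SD² × (1 − R²)], averaged over B ~ Beta((N − 2)/2, 1/2).

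**Step 1. Reproduce the plan's figure.** With 0.6 entered as R²:
- Residual variance = 81 × 0.40 = 32.4; at N = 156, λ = 39 × 9 / 32.4 = 10.83.
- 77 per arm gives 89.9% and 78 per arm gives 90.3%, so 78 is the smallest size that reaches 90%.
- 156 / 0.85 = 183.5, rounded up to 184. The drop-out step is correct.
- R² = 0.6 corresponds to r = √0.6 = 0.77.

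**Step 2. Use 0.6 as a correlation, as 9.4 states.** R² = 0.36.
- Residual variance = 81 × 0.64 = 51.84, residual SD = 7.2; at N = 156, λ = 351 / 51.84 = 6.77.

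| Per arm | Power, r = 0.6 | Power, R² = 0.6 |
|---|---|---|
| 78 (156 analysed) | 73.1% | 90.3% |
| 92 (184 analysed) | 80.0% | 94.4% |
| 123 (246 analysed) | 90.1% | 98.4% |

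- At r = 0.6, 122 per arm gives 89.9%, so 123 is the smallest size for 90%.
- Normal approximation as a check: n per arm = 2 × (1.960 + 1.282)² × 51.84 / 9 = 121.0, against 75.7 if the residual variance is 32.4.
- Difference detectable with 90% power at 78 per arm: the standard error is 7.2 × √(2/78) = 1.153, and 3.24 × 1.153 = 3.74. The exact method gives 89.6% power at 3.75 points and 90.4% at 3.8 points, hence about 3.8.

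**Step 3. Other explanations for 78 per arm.** At r = 0.6, by the normal approximation, 90% power needs:
- one-sided test: 99 per arm;
- change score instead of ANCOVA: 152;
- 3.4 points with SD 9: 95;
- 3 points with SD 7.4: 82;
- 3.4 points with the earlier trial's pooled SD: 89.

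Lowering the target to 80% power at the stated inputs needs 91. None of these gives 78.

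**Step 4. The Table 2 row on its own inputs.** Difference = 11.5 − 8.1 = 3.4. Pooled SD = √[(7.4² + 9.9²)/2] = 8.74. At r = 0.6 the power is 85.3% with 78 per arm and 90.5% with 92 per arm.

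**The case against.** **The analysed number may exceed 156.** Section 9.9 fills a missing week-6 score from week 3, then month 3, so many drop-outs would still enter the primary analysis. This stands. The fair figure is a range, 73 to 80%, and quoting 73% alone takes the least favourable end.

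**Other covariates add precision.** Section 9.3 also adjusts for diagnostic group, sex and age. If total R-squared reached 0.50, power would be 83% at 78 per arm and 89% at 92. This stands as a caution against reading 73% as the trial's actual power: it is the power at the inputs that 9.4 states. It does not rescue the 90%, because 9.4 ties 0.6 to the pre and post measurements alone and no section gives a value for the other covariates.

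**The cause is not proved.** A reader might infer that the protocol shows the correlation was typed in place of its square. It does not. The match in step 1 is exact and uses the named method, but another error, taking the 0.64 reduction twice, also lands near 78 by the normal approximation: 2 × 3.24² × 81 × 0.64² / 9 = 77.5. What is established is that the stated inputs do not give the stated size.

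**Table 2 already supports 90%.** A reader might conclude that the 90% in Table 2 should be replaced by 73%. The document does not support that. The row lists a different effect and spread, and at the 92 per arm it displays, 90% is compatible with r = 0.6. What remains is an ambiguity: the header speaks of 15% attrition, and with 78 per arm the row's own inputs give 85%.

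**The pass rule in 9.5 is not a significance test.** It asks for an observed difference of at least 3 points, which a true difference of exactly 3 would meet about half the time whatever the power. This is true, but the power claim in 9.4 concerns the test of the primary endpoint and is wrong independently of 9.5.

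**Conclusion.** The power statement in 9.4 does not follow from its inputs. At 3 points, SD 9, r = 0.6 and two-sided 5%, power is about 73% with 156 analysed and 80% with all 184 analysed, against 90% stated. The chance of missing a true 3-point effect is about 20 to 27%, not 10%. Reaching 90% would take 123 per arm (246 / 0.85 = 289.4, so 290 randomised). Entry of 0.6 as R-squared is the likely explanation, but it is an inference.

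The figures rest on one baseline covariate and the SD and correlation as stated. Nothing in the protocol supports a correlation of 0.77. Section 6.3 shows that the baseline and week-6 questionnaires differ in recall period and response wording, which gives no reason to expect a higher value than 0.6, but it does not tell us the actual correlation either. As illustrations only, r = 0.5 would give 66% at 78 per arm and r = 0.3 would give 58%.

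A reader might also infer that the trial must enrol more. That does not follow: 138 participants were already included by April 2023 (9.6), and the need is for an honest statement of power.

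**What to change.** In 9.4, do one of two things:
- keep r = 0.6, and state that power for 3 points is about 73% with 156 analysed and 80% with 184 analysed, and that about 3.8 points is detectable with 90% power at 78 per arm; or
- if R-squared of 0.6 was meant, write that (r = 0.77), say which covariates it covers, and give its source.

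In the VSS-SF row of Table 2, leave out the 3-point figures. State the difference, SD, correlation and analysed number behind the 90%. At r = 0.6 its own inputs give about 85% at 78 per arm, and 90.5% only if all 92 per arm are analysed.

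Optionally, estimate the SD and correlation from pooled data without arm labels (129 participants had reached week 6 at the time of the check in 9.6) and report the power at those values.

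The cost is a rewording of one paragraph and one table row, and a less favourable stated power. No extra enrolment and no change to the analysis are needed.
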